## 8.2 Rationale for study design

The European Medicines Agency (EMA) guideline on strategies to identify and mitigate risks for FIH and early clinical trials with IMPs (EMA/CHMP/SWP/28367/07 Rev. 1) has been considered as have the European Directive 2001/18/EC on the deliberate release into the environment of GMOs and the guidance on the environmental risk assessment of genetically modified organisms from the EMA CHMP/GTWP/125491/06. A 5-year long-term follow-up has been included in line with the recommendations given in EMA/CHMP/GTWP/60436/2007.

The SAD/MAD design of the study is based on the aim to study safety, tolerability and exposure of selected doses of activated ILP100-DP in a limited number of healthy volunteers.

The design is adaptive to allow for flexible dose escalation and involves careful monitoring of the subject's well-being. The study will provide important safety and tolerability data and preliminary efficacy data to support the design of further studies, both in healthy volunteers and in patients.

A placebo control will be used to establish the frequency and magnitude of changes in endpoints that may occur in the absence of active treatment. Subjects will serve as his/her own control receiving both placebo and active treatment on the same occasion. The placebo component consist of the ILP100-DP dilution buffer and the activation peptide SppIP. The dilution buffer contains sucrose, which may have a wound healing effect. Recombinant CXCL12 is not used as placebo since the half-life is too short (approximately 6 seconds) to provide clinically relevant data (Laguri *et al.*, 2007; Lambeir *et al.*, 2001). *Lactobacillus* wild-type is not used as placebo since extensive testing in non-clinical studies have shown that it has no effect on wound healing.

Saline (0.9 % NaCl) will be used as a “no treatment” control for several purposes, 1) all wounds must be treated with a solution to keep the blind, 2) all wounds must be exposed to comparable moisture during the study since moisture is a parameter that affects wound healing and 3) NaCl will identify any wound healing properties of sucrose in the dilution buffer used for both ILP100-DP and placebo.

Randomization will be used to minimize bias in the assignment of treatments to wounds.

Blinded treatment will be used to reduce potential bias during data collection and evaluation of endpoints.

All subjects in the MAD part will be treated at 10 dosing occasions over 3 weeks despite wound healing status. For this FIH study with focus on safety, and in order to obtain the same exposure time for all subjects, this approach was chosen rather than to continue treatment only until wound healing is achieved.

## 8.3 Selection of starting dose and rationale for planned dose escalation

### 8.3.1 Selection of starting dose and rationale for dose escalation

The dose is determined per area of the wound and is given in the unit colony forming units (CFUs) per cm^2.

The planned starting dose of activated ILP100-DP in the SAD part ( $5 \times 10^4$  CFU/cm^2 wound area) has been selected to give an adequate safety margin based on the preclinical studies. The planned doses to be administered in cohorts 2 and 3 of the SAD are  $5 \times 10^7$  and  $1 \times 10^9$  CFU/cm^2 wound area.

The highest dose used in non-clinical studies in mice with uncovered wounds was to  $2 \times 10^{10}$  CFU/cm^2. The highest dose used in the non-clinical work in minipigs with covered wounds was  $1.1 \times 10^{10}$  CFU/cm^2. No treatment-related systemic or local effects have been detected at any dose level tested. The SAD starting dose of  $5 \times 10^4$  CFU/cm^2 wound area is 400 000 times less the maximum dose given to mice and 220 000 times less the maximum dose given to minipigs (Table 8.3-2).

The lowest dose of  $5 \times 10^4$  CFU/cm^2 wound area in the SAD part has been selected based on the hypothesis that this dose will be outside the lower spectrum of the therapeutic window. This is based on experiments in mice where  $3.3 \times 10^2$  CFU/cm^2 failed to accelerate wound healing. The working hypothesis is that  $5 \times 10^7$  CFU/cm^2 is a therapeutic dose and the highest dose of  $1 \times 10^9$  CFU/cm^2 is 11 times lower than the highest dose given to minipigs ( $1.1 \times 10^{10}$  CFU/cm^2) at which no toxicity effects were detected. On a total dose basis (CFU/m^2 body surface are [BSA]), the highest dose to be administered in the SAD is 517 times lower than that administered in minipigs (Table 8.3-2). The total dose of the SppIP (ng/m^2 BSA) to be administered in the SAD is 42 times lower than that administered to minipigs. Hence, the human safety margin is considered sufficient.

The preliminary starting dose in the MAD part ( $5 \times 10^5$  CFU/cm^2 wound area) has been chosen based on the assumption that the  $5 \times 10^4$  CFU/cm^2 wound area dose, given as starting dose in the SAD part, will be non-efficacious. The starting dose in the MAD part will be finally set once the iSRC has evaluated the safety and tolerability data from the SAD part. The planned doses to be administered in cohorts 2 and 3 of the MAD are  $5 \times 10^7$  and  $1 \times 10^9$  CFU/cm^2 wound area. Doses in the MAD will be applied to the wounds approximately 3 times a week during 3 weeks (in total 10 doses).

Depending on the results in the SAD part the dose range might be narrowed in the MAD part to better capture differences and understand what dose is the most likely to have profile suitable for a therapeutic dose. If the  $5 \times 10^4$  CFU/cm^2 dose in the SAD part indicates an efficacy similar to the other doses, the lowest dose in the MAD part will be changed to  $5 \times 10^3$  CFU/cm^2. In case of no, or a small effect of the  $5 \times 10^4$  CFU/cm^2 dose in the SAD (which is the expected scenario), the starting dose in the MAD part will be  $5 \times 10^5$  CFU/cm^2.

For a summary of the planned doses in the present study, see Table 8.3-1. The administered volume of IMP is always 50 µL.

For further details on the prerequisites for the transition from single to multiple dosing, refer to Section 8.4.2.

**Table 8.3-1 Overview of intended dosing of ILP100-DP (CFU/mL CFU or ng SppIP/wound, cm^2 of wound surface and per BSA)**

| Cohort           | Wound area (cm  ) | Treated wounds/ Total no of wounds | Material            | Volume applied per wound µl | CFU/wound ( L. reuteri ) | CFU/ cm  ( L. reuteri ) | Exposure per body surface CFU ( L. reuteri )/ m  BSA |
|------------------|-------------------------------|------------------------------------|---------------------|-----------------------------|---------------------------------|--------------------------------------------|-------------------------------------------------------------------------|
|                  |                               |                                    |                     |                             | ng/wound (SppIP)                | ng/cm  (SppIP)                 | ng SppIP/ m  BSA                                            |
| 1 SAD            | 0.28 Ø 6 mm                   | 2/4                                | ILP100-DP activated | 50                          | 1.4x10              | 5x10                           | 1.7x10                                                      |
|                  |                               |                                    |                     |                             | 5                               | 18                                         | 6.2                                                                     |
| 2 SAD            | 0.28 Ø 6 mm                   | 2/4                                | ILP100-DP activated | 50                          | 1.4x10              | 5x10                           | 1.7x10                                                      |
|                  |                               |                                    |                     |                             | 5                               | 18                                         | 6.2                                                                     |
| 3 SAD            | 0.28 Ø 6 mm                   | 2/4                                | ILP100-DP activated | 50                          | 2.8x10              | 1x10                           | 3.5x10                                                      |
|                  |                               |                                    |                     |                             | 5                               | 18                                         | 6.2                                                                     |
| 1 MAD (10 doses) | 0.28 Ø 6 mm                   | 4/8                                | ILP100-DP activated | 50                          | 1.4x10              | 5x10                           | 3.5x10                                                      |
|                  |                               |                                    |                     |                             | 5                               | 18                                         | 12.3                                                                    |
| 2 MAD (10 doses) | 0.28 Ø 6 mm                   | 4/8                                | ILP100-DP activated | 50                          | 1.4x10              | 5x10                           | 3.5x10                                                      |
|                  |                               |                                    |                     |                             | 5                               | 18                                         | 12.3                                                                    |
| 3 MAD (10 doses) | 0.28 Ø 6 mm                   | 4/8                                | ILP100-DP activated | 50                          | 2.8x10              | 1x10                           | 6.9x10                                                      |
|                  |                               |                                    |                     |                             | 5                               | 18                                         | 12.3                                                                    |

\*Body surface area (BSA) = 1.6 m^2

### 8.3.2 Maximum exposure and dose

In the 4-week repeated dose toxicity study in minipigs, 3 levels of exposure of the *L. reuteri* R2LC expressing CXCL12 were used, see Section 6.1.6. There was no treatment-related toxicity detected at any of the dose levels used (Section 6.1.6). The highest dose given to minipigs was 1.1x10^10 CFU/cm^2.

The dose margins between the highest dose given to mini pigs (1.1x10^10 CFU/cm^2) and the proposed starting doses and maximum doses in the SAD and MAD parts, respectively are outlined in Table 8.3-2. The maximum dose of activated ILP100-DP to be administered in the present study is 1x10^9 CFU/cm^2 wound area.

**Table 8.3-2 Dose margins between high dose animals of the minipig study and the proposed starting and final doses of the SAD and MAD parts**

| Dose Parameter         | SAD                    |            | MAD                   |            |
|------------------------|------------------------|------------|-----------------------|------------|
|                        | Starting Dose          | Final Dose | Starting Dose         | Final Dose |
| CFU/cm     | 220 x 10   | 11         | 22 x 10   | 11         |
| CFU/m  BSA | 10.6 x 10  | 517        | 517 x 10  | 260        |

## 8.4 Dose escalation strategy

An adaptive dosing strategy will be applied to allow for flexible and safe dose escalation. Refer to Section 8.3.1 for the planned dose escalation.

Intermediate dose levels and/or additional dose groups may be considered if recommended by the iSRC (Section 8.4.3). The actual doses given will be guided by the iSRC recommendations and available safety and tolerability data will determine whether or not to follow the above provisional dose levels. Every dose step is thus adjustable.

Depending on results obtained during the study, the number of dose levels/regimens and planned sampling times might have to be adjusted. These adjustments will be documented in non-substantial amendments to the clinical study protocol (CSP).

### 8.4.1 *Stopping criteria for dose escalation*

The Principal Investigator and the iSRC (Section 8.4.3) will follow the recommendations and grading system of Common Terminology Criteria for Adverse Events (CTCAE) v5.0, see Section 11.7.1.7 but also take into account the recommendations published by Sibille *et al.* 2010, which is an adaptation to FIH studies of the grading systems previously proposed by National Cancer Institute (NCI), World Health Organization (WHO), National Institute of Health (NIH) and the US Food and Drug Administration (FDA). The grade, the frequency of AEs and the blindness will be considered.

A rolling review of emerging safety data will be performed throughout the study taking into account any AEs and their relation to pharmacodynamic (PD) effects, the number of subjects in whom they occur, concurrency of more than one event within the same subject and any trends. Changes from baseline measurements will also be considered and not just absolute cut-off based on upper- or lower limits of normal that might apply for healthy volunteers.

Trends or safety signals described above, which are not necessarily covered by the stopping criteria in Table 8.4-1 may warrant the scheduling of ad hoc iSRC meetings after which the iSRC will make recommendations to Sponsor on e.g. whether to terminate the study or to stop dosing in individual subjects or a certain cohort.

Stopping criteria related to exposure (area under the curve [AUC] and maximum plasma concentration [ $C_{max}$ ] of CXCL12) are considered as not applicable for the study since the systemic exposure of CXCL12 is predicted to be very low or undetectable.

**Table 8.4-1 Dose escalation and stopping rules**

| Level                                                                                                                                                                                               | Action taken                                                                                                                                                                                                                                                                                                                                                                                                                                                                                                                                                                                                                                                                                                                                                                                                                                     |
|-----------------------------------------------------------------------------------------------------------------------------------------------------------------------------------------------------|--------------------------------------------------------------------------------------------------------------------------------------------------------------------------------------------------------------------------------------------------------------------------------------------------------------------------------------------------------------------------------------------------------------------------------------------------------------------------------------------------------------------------------------------------------------------------------------------------------------------------------------------------------------------------------------------------------------------------------------------------------------------------------------------------------------------------------------------------|
| If no subject has an SAE considered at least possibly related to the IMP administration, i.e. a serious adverse drug reaction (SADR)                                                                | Escalate to the next higher dose level.                                                                                                                                                                                                                                                                                                                                                                                                                                                                                                                                                                                                                                                                                                                                                                                                          |
| If 1 subject has an SAE assessed as at least possibly related to IMP administration                                                                                                                 | 
 
1) Stop of further dosing at this dose level
 
2) If the SAE is clearly associated with a single, or multiple wound(s): unblinding of these wounds. Only voting members of the iSRC will be unblinded.

If the etiology of the SAE is not obviously associated with a single, or multiple, wound(s), no unblinding will be performed. The SAE will be regarded as related to ILP100-DP.
 
3) Evaluation by iSRC. The iSRC makes recommendation to Sponsor.

Subject meets stop criterion: stop further dosing at this dose level for all subjects. Sponsor decides if the study will be terminated or if dosing will commence at a lower dose level or at an intermediate dose level.
 
                                                                            |
| If 2 subjects on active treatment have severe, non-serious AEs assessed at least possibly related to the IMP administration (independent of within or not within the same System organ class [SOC]) | 
 
1. Stop dosing of subjects with severe, non-serious potential ADRs.
 
2. If the AEs are clearly associated with a single, or multiple wound(s): unblinding of these wounds. Only voting members of the iSRC will be unblinded.

If the etiology of the AEs is not obviously associated with a single, or multiple, wound(s), no unblinding will be performed. The AEs will be regarded as related to ILP100-DP.
 
3. Evaluation by iSRC. The iSRC makes recommendation to Sponsor.
 
4. Sponsor decides how to proceed:

Both subjects meet stop criterion: stop further dosing at this dose level for all subjects. Sponsor decides if the study will be terminated or if dosing should commence at a lower dose level or at an intermediate dose level.
 
 |
| If 2 subjects in different cohorts have SAEs assessed as at least possibly related to IMP administration                                                                                            | 
 
1. Stop dosing of subjects with potential SADR.
 
2. If the SAEs are clearly associated with a single, or multiple wound(s): unblinding of these wounds. Only voting members of the iSRC will be unblinded.

If the etiology of the SAEs is not obviously associated with a single, or multiple, wound(s), no unblinding will be performed. The SAEs will be regarded as related to ILP100-DP.
 
3. Evaluation by iSRC. The iSRC makes recommendation to Sponsor.

Both subjects meet stop criterion: Termination of study.
 
                                                                                                                                                                                                                                      |

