### **General**

The investigator will assess local tolerability, wound healing and scar formation by direct observation. The subjects will assess local tolerability (pruritus and pain). Three to five independent experts will assess local tolerability, wound area, wound healing and scar

formation by using the wound/scar photographs. For details on timing of assessments, refer to Table 8.1-2.

Before initiating a new cohort, all subjects in the previous cohort must have been treated and 21 days safety and tolerability data for all treated subjects must have been evaluated by the iSRC, see Section 8.4.3. Once Day 21 safety and tolerability data for the last subject in each cohort has been collected, there will be at least 1 week between dose escalations.

Each subject is expected to participate for approximately 49 days (including a 28-day screening period) in the first phase of the MAD part and for an additional 5 years in the long-term follow-up.

The schedule of events is shown in Table 8.1-2. Study assessments are described in Section 11.

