#### 8.4.3 *Internal safety review committee*

Before initiating a new cohort, all subjects in the previous cohort must have been treated and 3 days (SAD) and 21 days (MAD) safety and tolerability data for all treated subjects must have been evaluated by the iSRC. Based on emerging safety and tolerability data, the amount of required safety data to be reviewed after a completed cohort might be adjusted. Details regarding timing of iSRC review and the data to be reviewed and the documentation procedure will be provided in a separate iSRC charter.

The voting members of the iSRC will consist of the Principal Investigator, the Medical Monitor (i.e. the Sponsor's medically responsible person) or delegate and an independent, external clinical expert. The clinical research manager (CRM), and additional Sponsor representatives will be invited as appropriate. Further internal or external experts may be consulted by the iSRC as necessary.

An adaptive dosing strategy will be applied to allow for a flexible and safe dose escalation. The planned dose escalation is outlined in Section 8.3.1. The actual doses given in each cohort will be guided by the iSRC recommendations based on available safety and tolerability data. Every dose step is thus adjustable and the recommendation to the Sponsor may be to continue with a higher or lower dose than the intended dose, repeat the same dose level, continue with an intermediate dose level or to stop dosing.

The decision of the iSRC on the recommendation of the next dose level will be taken in consensus between the iSRC members and documented as appropriate. In case there is disagreement between the 3 voting members, the most conservative approach will be taken. It is not acceptable to repeat a dose level where any of the dose escalation stopping rules have been met.

The treatment code for individual wounds may be broken by the iSRC during the assessment process (partial un-blinding) in accordance with stopping criteria described in Table 8.4-1. The medical staff and the subjects will still be blinded for the treatments (active drug, placebo or saline) to be administered in the subsequent dose groups/cohorts in order to minimize bias. If unblinding was considered necessary, the iSRC meeting may consist of a closed part and an open part.

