## 9.10 Blinding

This is a double-blind study and the allocation of treatments will not be disclosed to clinical staff involved in study-related evaluations nor to independent evaluators until the 12 months long-term follow-up visit in each part has been conducted.

The activated ILP100-DP is a pale-yellow to yellow solution. Placebo and saline are transparent solutions. Every effort will be made at the research clinic in order to maintain the blind. Both the activated ILP100-DP, the placebo and the saline solutions will be masked in such a way that study subjects and study staff will remain blinded during the study. An unblinded pharmacist will prepare the activated ILP100-DP/placebo/saline under supervision of an unblinded study nurse or delegate. The procedure will be documented by video recording. Unblinded staff will also apply the IMP, see Section 10.6. The unblinded staff will not be involved in any study-specific evaluations (study-specific evaluations do not include sample handling). Once the adhesive film has been applied on each wound it is not possible to distinguish between the treatments.

The subjects will be blindfolded during the administration procedure.

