## 16.7 Database lock

When all data have been entered and discrepancies solved, clean file will be declared, the database will be locked, the code will be broken and the data will be analyzed.

Interim reports based on unblinded data will be prepared after completion of the 6 weeks visit (Visit 7 [SAD part] and Visit 14 [MAD part] and after completion of the 12 months visits (Visit 10 [SAD part] and Visit 17 [MAD part]; one report with combined 12 months SAD and MAD data). The data for the reports will be produced from exports of the cleaned database but no formal DBL will be performed until after the last subject has performed the last 5-year follow-up assessment. A complete CSR including will be written following the final DBL.

All clinical staff involved in data evaluation and all independent evaluators will be kept blinded to treatment.

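### When a stopping-rule event is tied to a wound, the Principal Investigator may learn that subject's allocation, although the protocol promises that evaluating staff stay blinded

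*Protocol*

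**What the plan says.** Table 8.4-1 (Section 8.4.1) opens a treatment code only when the event can be linked to particular wounds. For the rule on one related serious adverse event (SAE) it reads: "If the SAE is clearly associated with a single, or multiple wound(s): unblinding of these wounds". The rules on two severe non-serious events and on two SAEs carry the same condition. Without an obvious link to a wound, no code is opened and the event is attributed to the active product. On who learns the code, the table says: "Only voting members of the iSRC will be unblinded".

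Section 8.4.3 names the voters: "The voting members of the iSRC will consist of the Principal Investigator, the Medical Monitor" (or a delegate), with an outside clinical expert as the third.

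Section 9.10 says that allocation "will not be disclosed to clinical staff involved in study-related evaluations nor to independent evaluators until the 12 months long-term follow-up visit" has taken place in each part. Section 16.7 adds: "All clinical staff involved in data evaluation and all independent evaluators will be kept blinded to treatment". Neither section mentions the iSRC as an exception.

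Sections 8.4.3 and 9.11 do foresee partial unblinding by the iSRC. What they then say about medical staff and subjects is that these remain blinded to treatments in cohorts still to come. They do not address the subject whose code was opened.

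The evaluator is the Investigator. Section 8.1.2 states for the multiple ascending dose (MAD) part: "The investigator will assess local tolerability, wound healing and scar formation by direct observation". Section 8.1.1 says the equivalent for the single ascending dose (SAD) part. Wound infection (7.1.1, 11.7.7) and adverse event (AE) causality (11.7.1.8) are also the Investigator's assessments. In long-term follow-up, local tolerability and scar tissue are assessed by the Investigator only (footnotes to Tables 8.1-1 and 8.1-2).

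**The concern.** The same person may hold two roles that the protocol means to keep apart: voter with access to the code, and blinded assessor of primary safety endpoints. Nothing removes an unblinded voter from later assessment of the same subject.

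Subjects are their own controls, so an assessor who knows which arm is active knows the direction of the whole within-subject comparison. The subject concerned is also the one who produced the safety signal, where later scores will be read most closely. Table 8.4-1 tries to contain the disclosure by opening only the affected wounds, but allocation by arm (Section 9.9) defeats that limit. The exposure matters most for infection, causality of new AEs, and local tolerability and scars from the 6-week visit on, because no photograph evaluator backs these up.

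**Working it through.** The plan states no figure on this point, so the check has two steps: compare the passages, then list the allocation layouts.

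**Step 1: the passages side by side**

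| Question | Protocol text | Answer |
|---|---|---|
| When is a code opened? | Table 8.4-1 | Only if the event is clearly linked to wounds |
| Who sees it? | Table 8.4-1 | Voting iSRC members |
| Does that include the Principal Investigator? | 8.4.3 | Yes, one of three voters |
| Who scores wounds, infection and AE causality? | 7.1.1, 8.1.1, 8.1.2, 11.7.1.8, 11.7.7 | The Investigator; the Principal Investigator is not excluded |
| Must evaluating staff stay blinded? | 9.10, 16.7 | Yes, with no exception; 9.10 sets the 12-month visit as the end |
| Is the unblinded subject's later evaluation protected? | 8.4.3, 9.11 | Not addressed; only later cohorts are |

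If the Principal Investigator evaluates, the fourth and fifth rows cannot both be met once a code has been opened.

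**Step 2: what one opened wound reveals about the same subject**

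Inputs: Section 9.9 (randomization by arm; 2 wounds per arm in SAD; in MAD, 4 active wounds on one arm and 2 placebo plus 2 saline on the other) and Table 9.9-1 (an example with placebo and saline in adjacent pairs).

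For each layout, keep those compatible with the opened wound and count the wounds whose treatment is the same in all of them.

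| Part and layout | Possible layouts | Opened wound | Still compatible | Wounds known exactly | Active and control arm known |
|---|---|---|---|---|---|
| SAD | 2 | active or placebo | 1 | 4 of 4 | yes |
| MAD, pairs as in Table 9.9-1 | 2 × 2 = 4 | active | 2 | 4 of 8 | yes |
| MAD, pairs as in Table 9.9-1 | 4 | placebo or saline | 1 | 8 of 8 | yes |
| MAD, free placement on control arm (assumption) | 2 × 6 = 12 | active | 6 | 4 of 8 | yes |
| MAD, free placement on control arm (assumption) | 12 | placebo or saline | 3 | 5 of 8 | yes |

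Active versus control status is therefore known for all wounds in every case. In MAD, an opened active wound leaves placebo versus saline undetermined.

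**Share of a cohort.** Cohorts have 4 subjects (SAD) or 8 (MAD). One subject is 1/4 = 25% or 1/8 = 12.5%. Two subjects in one cohort are 2/4 = 50% or 2/8 = 25%. The two-subject share can arise only under the severe-event rule, and only if both subjects are in the same cohort and both events are tied to wounds. The two-SAE rule concerns different cohorts, so each has one such subject.

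**The case against.** The strongest reply is that the exception was intended. Section 9.11 follows directly on 9.10 and provides for iSRC unblinding, so the specific provision can be read as qualifying the general one. The sentence in 16.7 closes a passage on interim reports and database lock. Section 8.4.3 allows closed and open meeting parts and leaves detail to a charter that is not at hand. Another investigator on the team could do the scoring. This stands in part: the partial unblinding is deliberate, and its scope is small. It does not settle who evaluates the unblinded subject afterwards, and a closed session does not keep the code from the Principal Investigator, who is a voter.

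A reader might also infer more than the text supports:

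- *Any stopping-rule event unblinds the Principal Investigator.* It does not; the event must be clearly tied to a wound.
- *The blind is lost for five years.* Section 9.10 promises it only to the 12-month visit, so later years are not part of the conflict.
- *The primary local-reaction scores become open-label.* During the treatment phase, 3 to 5 independent evaluators score the same seven parameters from photographs, and subjects rate pain and pruritus. None of them is shown the code. Only the Investigator's parallel scores and the Investigator-only assessments are exposed.
- *The causality call that fires the rule is biased.* That call comes before any code is opened; only later AEs in that subject are affected.
- *The Principal Investigator should be denied the code.* Under 8.4.3, disagreement among the three voters resolves to the most cautious option. A voter without the code could therefore decide the outcome merely for lack of it. That is a debatable trade-off, not a clear improvement.

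**Conclusion.** The concern holds in limited form. The access given by Table 8.4-1 and Section 8.4.3 conflicts with the unqualified promises in 9.10 and 16.7, and the wound-level limit does not contain the disclosure, because one opened wound identifies the active and control arms.

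What is exposed, for the affected subject and up to the 12-month visit, is the Investigator's later direct-observation scores, infection assessments and causality calls for subsequent AEs. The extent is one subject (25% of a SAD or 12.5% of a MAD cohort), or up to two if both severe-event subjects are in the same cohort.

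This rests on two conditions: an event clearly tied to a wound occurs, and the Principal Investigator also acts as evaluating Investigator. The second is a natural reading at a single centre, and the protocol neither requires nor excludes it. The point is contingent, but it touches primary safety assessments and is worth correcting.

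**What to change.** Reconcile Sections 8.4.1, 8.4.3 and 9.11 with 9.10 and 16.7 through two wording changes:

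1. In 9.10 and 16.7, state that voting iSRC members may learn the code of individual wounds under Table 8.4-1, with a cross-reference to 8.4.3 and 9.11.
2. In 8.4.3, and in the iSRC charter, add that any voting member shown a subject's code does not afterwards score that subject's wounds or scars, or assign AE causality for that subject, before the 12-month visit. A still-blinded investigator already on the site team takes these over.

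All three voters remain fully informed, and no dose, stopping threshold or voting right changes. The cost is wording, delegation of one or two subjects' assessments, and a possible change of rater within those subjects, which should be recorded. Because the Medical Monitor also votes and gives a causality assessment for SAEs (11.7.1.12), the sponsor would need a blinded delegate for that task in the same subject.
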